### Interim analyses {21b}

There are no interim analyses planned.

### Methods for additional analyses (e.g. subgroup analyses) {20b}

There are no subgroup analyses planned.

### Methods in analysis to handle protocol non-adherence and any statistical methods to handle missing data {20c}

Data will be explored for structural missingness and reported accordingly. The primary population under investigation will be the modified intention to treat (ITT). The ITT population will be defined as all children with at least one post baseline timepoint.

### Plans to give access to the full protocol, participant-level data and statistical code {31c}

Following 1 year after the end of the study researchers may request access to the study data. Any request should be made with a statistical analysis plan addressing a specific research question not answered by the CUES for schools trial. All requests are made to the corresponding author and approved by the CUES trial management group. Statistical code for the primary analysis will be provided upon request.

## Oversight and monitoring

### Composition of the coordinating centre and trial steering committee {5d}

Data monitoring will be the responsibility of the study research lead (SJ), overseen by the trial management group and the steering committee. As data will be collected over a relatively short period of time, there will be no interim analyses. As we do not anticipate risks to participant safety as a direct result of the study and will not be conducting any interim data analysis, we will not convene a separate Data Monitoring Committee (DMC) and will devolve these functions to the trial steering committee (TSC) which will be detailed in the TSC charter. The study will be subject to the standard local and national governance frameworks of SLaM Research & Development, CAMHS clinical services and research coordination, and our ethics committee.

An independent trial steering committee will be established to oversee trial conduct.

### Composition of the data monitoring committee, its role and reporting structure {21a}

We will hold a combined TSC and DMC with a member of the DMC monitoring safety events split by arm at their request and reporting any concerns for the continuation of the study to the TSC during the meetings.

### Adverse event reporting and harms {22}

#### Harms

We will ask teachers to report to the study team any concerns about CUES or the assessment protocol or any other aspect of the study, expressed by teachers themselves, parents, or children. These will be reviewed by the steering committee for severity, and attributability to the study in liaison with the school, and parents if relevant.

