**Methods:**

The “CUES for Schools” study is a multicentre cluster randomised controlled trial in primary schools in south east England. Schools will be randomised to receive the usual school curriculum, or the CUES programme (1:1). We aim to enrol 74 schools (5550 children including 2220 vulnerable children). CUES is a whole-class teacher-facilitated interactive digital cognitive-behavioural intervention, delivered as 24 short (20-min) modules over 12 weeks, targeting emotional/behavioural regulation skills. Children self-report emotional/behavioural problems at baseline, 8, and 16 weeks, and wellbeing and cognitive vulnerability at 0 and 16 weeks. Adverse events are assessed at 8 and 16 weeks. Teachers rate classroom behaviour at baseline and 16 weeks. School senior leadership teams and individual teachers consent to involvement in the study; parents can opt their child out of CUES sessions, assessments, or research. Children can similarly opt out and assent to research participation. The primary objective of this trial is to evaluate the effectiveness of CUES for schools compared to the usual school curriculum in improving emotional/behavioural problems for vulnerable Year 4 (8–9 years old) children at 16 weeks post-randomisation, as measured using a standardised questionnaire designed for primary schools. The secondary objective is to investigate the impact of the CUES for schools programme on both vulnerable and non-vulnerable children on wellbeing and teacher-rated classroom behaviour.

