### Intervention description {11a}

*CUES* comprises seven modules, with 24 lessons delivered over 12 weeks (within a 16-week window), in sessions of 20 min, two or three times/week. Schools will be asked to incorporate CUES into their social and emotional learning provision, so children do not have additional time in the classroom. The programme consists of digital interactive sessions. Teachers guide their class through the sessions using the content and interactivities that are part of the package. The package incorporates branding and characters designed to be appealing and engaging, in a mix of animation and video. Children in the intervention arm will receive CUES straight away. Children in the WL arm will receive CUES later in the term or in the following academic year.

For schools allocated to the CUES arm, teachers will watch the instructional video, and start the CUES programme. CUES delivery should start within 2 weeks of randomisation and proceed at an hour each week. There are 12 h of teaching to deliver within the 16-week window. Measures will be completed at baseline, T1 (8 weeks, primary outcome only) and T2 (16 weeks) in both arms.

The end of the trial will be defined as the last follow-up assessment at T2. WL participants will then receive CUES, at a time suitable in the context of the usual curriculum. This will not be part of the outcomes of the study and children will not be asked to complete any further measures.

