## Data collection and management

### Plans for assessment and collection of outcomes {18a}

Outcome measures (child emotional/behavioural problems, child wellbeing, teacher-rated class behaviour) will be completed by children and teachers at T0, T1 (primary outcome only), and T2, on paper, with support from a research worker online or in-person as required. Measures will be completed as a group in the classroom. Assessments should occur within a 6-week window of their calendar date (up to 2 weeks earlier or up to four weeks later), counted from the day of randomisation. Assessments will be collected by teachers and returned securely by courier to the research team.

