Data completeness was good (primary outcome missing for 2% of children at baseline, < 1% at follow-up; 0–11% missing data for single items on secondary outcomes, mode = 0), indicating children found the assessments acceptable. Completing all measures at three time points elicited informal feedback of fatigue at repetition. In response, we now ask for only the primary outcome at T1 (8 weeks). Measures are self-report by children and teachers. While standardised measures are designed and well-validated for school use with this age group, there is potential for bias as neither children nor teachers can be blinded to allocation. Thus, the self-report nature of the assessments may offer a limitation. Previous authors have argued that the waiting list control may artificially inflate the between-group difference [24]. It should be noted the same effect was seen in the clinical service evaluation as within the feasibility study point estimate, which may not support this. The same teachers that delivered the CUES for schools lessons to the children carried out the teacher-rated assessments — so this outcome may suffer assessor-rated bias.

The programme is designed to improve emotional/behavioural problems specifically for vulnerable children participating within whole class groups. Service data has shown small, yet consistent improvements, which were replicated in feasibility data. Given the mixed outcome data for vulnerable children taking part in similar programmes in schools to date [9, 10], reliably improving their outcomes is a key public health priority. A significant strength is that the programme can be delivered by teachers without extensive additional training. The training provided is integral to the platform except for a short instructional video on presentation style. Implementability should therefore be high, addressing concerns about the continued rollout of research-based initiatives [13].

While the platform content is set, teachers are free to adapt their own delivery to accommodate local variations in context and cultural needs. The recruitment areas are socio-economically diverse, and the programme is designed to be suitable for all schools irrespective of size or setting.

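### The abstract promises adverse-event assessment at 8 and 16 weeks, but the body provides only unscheduled, teacher-relayed concerns about the study, so equal ascertainment in the two arms is not assured

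*Protocol article*

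**What the plan says.** The abstract (Methods) gives a schedule for harms: "Adverse events are assessed at 8 and 16 weeks".

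The Harms section under {22} describes a different procedure. It begins "We will ask teachers to report to the study team any concerns about CUES or the assessment protocol" and continues "or any other aspect of the study, expressed by teachers themselves, parents, or children". On review it says: "These will be reviewed by the steering committee for severity, and attributability to the study in liaison with the school, and parents if relevant". It gives no time point, set question or definition of an event, and it does not distinguish between arms.

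On the content of the 8-week contact, Intervention description {11a} says: "Measures will be completed at baseline, T1 (8 weeks, primary outcome only) and T2 (16 weeks) in both arms". Plans for assessment and collection of outcomes {18a} lists child and teacher outcome measures that "will be completed by children and teachers at T0, T1 (primary outcome only), and T2". The Discussion repeats that restriction and explains it by children's fatigue with repeated measures. In Table 1 the only assessment marked at 8 weeks is Me & My Feelings (M&MF), and no row concerns adverse events.

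On oversight, section {21a} provides for a data monitoring committee member "monitoring safety events split by arm at their request", who reports any worry about continuing the study to the trial steering committee. Section {5d} says there will be no separate data monitoring committee.

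**The concern.** There are two linked problems.

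The first is one of consistency. The abstract describes scheduled assessment at two time points. The section devoted to harms, the participant timeline and the descriptions of the 8-week visit do not provide it. A school, a research worker or a steering committee member working from the body would not know that an adverse-event assessment was due at either time.

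The second concerns what the Harms procedure can support. It gathers concerns about the study. Before anything is reported, someone has to connect what happened to a child with the study. Attribution thus filters reports before the committee's own review of attributability begins. The filter need not act equally in the two arms. Teachers know the allocation, CUES teachers are delivering the programme, and waitlist teachers deliver nothing new before the 16-week assessment. A child who deteriorates in a waitlist school is less likely to be raised as a matter about the study. If the arms are then compared on these reports, a difference could reflect the opportunity to report, and a lack of difference could hide unequal capture.

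**Working it through.** The main check sets the passages side by side; no planned figure depends on this point.

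**Is the 8- and 16-week assessment provided anywhere outside the abstract?**

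| Place | 8 weeks | 16 weeks |
|---|---|---|
| Abstract, Methods | Adverse events assessed | Adverse events assessed |
| Table 1 | M&MF only | M&MF, CORS, teacher-rated outcomes, workbook measures |
| Intervention description {11a} | Primary outcome only | Measures completed; adverse events not named |
| Outcome collection {18a} | Primary outcome only | Child and teacher outcome measures; adverse events not named |
| Discussion | Primary outcome only | Adverse events not scheduled |
| Harms {22} | No time point | No time point |

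The abstract's statement has no counterpart in any of these places. At 8 weeks, a literal reading of three sections excludes it.

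**What does the Harms procedure ascertain, and from whom?**

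1. Object: concerns about CUES, the assessments or anything else in the study. Events in children regardless of a perceived link are not requested.
2. Channel: teachers, who also pass on what parents and children say. Section {17a} states that teachers cannot be blind to allocation.
3. Exposure: under {11a}, CUES schools deliver 24 lessons within the 16-week window, and waitlist schools receive CUES only after the 16-week assessment.
4. Study contact: the Discussion adds a weekly adherence check to help delivery stay on time. By its purpose this concerns schools that are delivering CUES. The document does not say that harms are collected through it.
5. Use: section {21a} foresees safety events viewed by arm.

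Items 1 to 4 make unequal capture possible. They do not establish it.

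**Can the size be calculated?**

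Let N be the children per arm, p a true event rate common to both arms, and c1 and c0 the proportions of events reported in the CUES and waitlist arms. The expected reports are N·p·c1 and N·p·c0, and their ratio is c1/c0.

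From Sample size {14}, 5550 children split equally gives N = 5550/2 = 2775. The document gives no value for p, c1 or c0. With an assumed p of 5%, the true events are 2775 × 0.05 = 138.75 per arm, and:

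- Equal capture (assumed 80% and 80%): 138.75 × 0.8 = 111 against 111, ratio 1.
- Unequal capture (assumed 80% and 40%): 111 against 138.75 × 0.4 = 55.5, about 56, ratio 2.

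The ratio only returns the assumed capture rates. It shows the mechanism and says nothing about the likely size in this trial.

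**The case against.** The strongest reply is that the texts can be read together: the abstract gives the timing and the Harms section gives the channel. Table 1 is not exhaustive, since child attendance and teacher adherence have no row either. The restriction at 8 weeks can be read as applying to outcome measures, because the reason given is fatigue at repeating them. A journal article also condenses a fuller protocol, where forms and definitions usually sit.

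Part of this stands. The absence of a form or a definition is not itself a fault here, and Table 1 alone would prove little. But the Harms section is where a scheduled assessment would be stated, and it describes something of a different kind: relayed concerns rather than events. That mismatch lies between passages that are present and does not depend on what the full protocol contains.

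A reader might also infer several stronger points, which the document does not support:

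- *Only concerns about CUES are sought.* The sentence extends to any aspect of the study and to concerns voiced by parents and children. Waitlist schools also take part in the study and its assessments.
- *Reporting is spontaneous.* Teachers will be asked. What is lacking is a schedule and a structured question.
- *There is no contact with teachers at 8 weeks.* Section {26a} has research workers completing assessments with children and teachers at all three time points, and {18a} has teachers collecting and returning the forms. What is absent at 8 weeks is a teacher measure.
- *Deterioration goes unrecorded.* M&MF is completed in both arms at 0, 8 and 16 weeks, its subscales are analysed in the whole school population, and {20a} summarises the proportion meeting the vulnerability criteria at each time point.
- *Relayed concerns are all the committee will see, so its comparison is worthless.* Section {5d} leaves its functions to a charter that is not shown, and it reviews each report for severity and attributability, not counts alone.
- *Under-counting or imbalance is certain.* Neither is shown. The Discussion reports no adverse events in the feasibility study or in service delivery.

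**Conclusion.** The point holds in limited form. The abstract's adverse-event assessment at 8 and 16 weeks is not provided for in the body of the article, and at 8 weeks it conflicts with the stated content of the visit on a literal reading. The Harms procedure collects study-related concerns through unblinded teachers, only some of whom are delivering the programme. Equal ascertainment is therefore not assured, and the by-arm review of safety events may be hard to interpret.

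No size can be attached to this. Any between-arm bias depends on unequal reporting, which the text makes possible but does not demonstrate. The conclusion assumes that the article's Harms section describes the procedure in substance; a fuller protocol with a structured event form used in both arms would remove the concern about ascertainment but leave the article's passages to be reconciled. The primary outcome analysis is untouched. The change should be made because a stated harms method and a planned safety review rest on it.

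**What to change.** Reconcile the abstract, Table 1, {11a}, {18a}, {22} and the Discussion.

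- **If scheduled assessment is intended:** put one identically worded adverse-event question to schools in both arms at 8 and 16 weeks. It should ask about events in children whether or not anyone sees a link to the study, and leave attribution to the steering committee. Add an adverse-event row to Table 1, state the two time points under {22}, and make clear that the 8-week restriction applies to outcome measures. The existing request for concerns can remain alongside it.
- **If it is not intended:** correct the abstract, and state under {21a} and {22} that counts of relayed concerns by arm are not a comparative safety measure.

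The first option costs one question, which can be returned with forms that teachers already collect at both times, one table row and a small extra form burden for teachers. The second costs only text.

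A by-arm table of initially non-vulnerable children who later cross the M&MF threshold could be added from data already collected. It is optional and corrects no stated error.

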#### Withdrawal of participants

Schools will have the right to withdraw from the study at any time up until the start of delivery for any reason. Once delivery has begun, both children and parents will also be involved and a school opt-out will need to take their wellbeing and expectations into account.

### Frequency and plans for auditing trial conduct {23}

The research data will be stored in King’s College London online servers. The Investigator(s) will permit trial-related monitoring, audits, research ethics committee (REC) review, and regulatory inspections by providing the Sponsor(s) and REC direct access to source data and other documents providing this is within the bounds of data protection and the protection of participants’ confidentiality.

### Plans for communicating important protocol amendments to relevant parties (e.g. trial participants, ethical committees) {25}

All substantial major protocol revisions will follow the King’s College Research Ethics Committee revision process and will be approved prior to their implementation. If a revision leads to a substantial change to the study design, e.g. adding an additional time-point, we will repeat our consent process to re-consent parents and children and allow them to opt out to the revised changes.

### Dissemination plans {31a}

Findings will be communicated to participating school SLTs, who will be free to choose the best method for their school for dissemination. We will present the findings of the research at conferences and will publish in peer-reviewed journals. Locally, we will present to services within our Academic Health Sciences Network, where we have close practice and training links.

## Discussion

The CUES for schools study will evaluate an interactive digital platform designed for teacher-facilitated delivery in primary school children. Trial procedures have been shown to be feasible, and in excess of 6000 children have received an expert-delivered version of the programme as part of local service delivery ([name] et al., personal communication).

This study will extend recruitment from inner London to outer London and the home counties. Feasibility study uptake was 11 of 36 eligible schools (30%) with 14 expressing interest. As we are recruiting across nearly 40 boroughs/counties, each with 40–80 eligible schools, we do not anticipate difficulty recruiting to our target of 74 schools and can increase this if insufficient numbers of vulnerable children are enrolled. No teacher declined participation. Our feasibility study employed a parental consent and child assent procedure: 8% of parents and 13% of children declined consent; just over 40% of parents and just over 75% of children returned a form and agreed participation. We anticipate higher parental return rates using an opt-out procedure. Parental and child requests to withdraw from delivery of the programme were low (*n* = 2), similar to in-service delivery, and child and teacher feedback in-service was consistent with acceptability, and safety, with no adverse events reported in the feasibility study, or during in-service delivery [5, 19]. Over 80% of children completing baseline assessments were retained in the feasibility study at follow-up.

Teachers varied in the timeliness of programme delivery in the feasibility study: we have implemented a weekly adherence check for this study to facilitate delivery within the 16-week window.

Data completeness was good (primary outcome missing for 2% of children at baseline, < 1% at follow-up; 0–11% missing data for single items on secondary outcomes, mode = 0), indicating children found the assessments acceptable. Completing all measures at three time points elicited informal feedback of fatigue at repetition. In response, we now ask for only the primary outcome at T1 (8 weeks). Measures are self-report by children and teachers. While standardised measures are designed and well-validated for school use with this age group, there is potential for bias as neither children nor teachers can be blinded to allocation. Thus, the self-report nature of the assessments may offer a limitation. Previous authors have argued that the waiting list control may artificially inflate the between-group difference [24]. It should be noted the same effect was seen in the clinical service evaluation as within the feasibility study point estimate, which may not support this. The same teachers that delivered the CUES for schools lessons to the children carried out the teacher-rated assessments — so this outcome may suffer assessor-rated bias.

The programme is designed to improve emotional/behavioural problems specifically for vulnerable children participating within whole class groups. Service data has shown small, yet consistent improvements, which were replicated in feasibility data. Given the mixed outcome data for vulnerable children taking part in similar programmes in schools to date [9, 10], reliably improving their outcomes is a key public health priority. A significant strength is that the programme can be delivered by teachers without extensive additional training. The training provided is integral to the platform except for a short instructional video on presentation style. Implementability should therefore be high, addressing concerns about the continued rollout of research-based initiatives [13].

While the platform content is set, teachers are free to adapt their own delivery to accommodate local variations in context and cultural needs. The recruitment areas are socio-economically diverse, and the programme is designed to be suitable for all schools irrespective of size or setting.

This is a large randomised controlled trial enrolling all children in consented schools in south east England across a range of socioeconomic areas and should offer generalisability. Given the feasibility work undertaken so far, we anticipate that the study will enrol the majority of children from each school enrolled as well as follow up the majority. There is potential to improve current functioning for children, as well as reducing future mental health burden, should CUES for schools prove effective.

